### Outcome measures

#### Primary outcomes

Our primary patient-level composite outcome is the number of days alive and ventilator-free (AVF) within the first 21 days after intubation or after PICU admission for patients intubated at an outside hospital. Days AVF within 21 days are defined as days when the patient was alive, and an endotracheal tube was absent for 24 continuous hours during a calendar day, ranging from 0 (any patient who experiences death prior to extubation or those intubated for more than 21 days) to 20 (patient is extubated the day following intubation and is alive by 21 days). If the patient was successfully extubated and discharged before 21 days, the days after discharge are ventilator-free. For patients discharged to a long-term ventilation rehabilitation facility, if such discharge happens before day 21, the patient will be considered to be mechanically ventilated for the remainder of the days to day 21. Days AVF was selected over the rank-based composite ventilator-free days given that expected mortality rates are relatively small and days AVF considers any day off the ventilator as important to the patient, family, and provider regardless of patient survival [4, 39–41].

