#### Process evaluation

A mixed-methods process evaluation will be performed using the UK’s Medical Research Council’s framework for evaluating complex interventions and guided by the Systems Engineering in Patient Safety 2.0 Framework (SEIPS 2.0; Preliminary Data) [44].

We will summarize the outcome of PICU Up! performance at the PICU level for each month of the intervention period. Specifically, we will calculate a measure of complete, proportional, and individual element performance for each PICU (Table 2). The monthly complete and proportional performance will respectively be defined as the proportion of patient days (for eligible patients) in which every eligible element of PICU Up! was performed and the proportion of eligible elements received divided by the number of eligible elements [34]. Individual performance will be defined as the proportion of patient days (for eligible patients) where the individual element was received divided by the number of days where the individual element was eligible.

**Table 2 Tab2:** Definition of PICU Up! performance measures [34]

Element	Days eligible	Performance
**A**	All days	≥ 6 pain assessments/24 h using a validated pediatric pain scoring scale
**B**	Days when receiving invasive mechanical ventilation	Screened for extubation readiness trial once daily if receiving invasive mechanical ventilation
**C**	Days when receiving sedation and/or invasive mechanical ventilation	≥ 6 sedation assessments/24 h using a validated sedation scale and sedation goal documentation if receiving sedation and/or invasive mechanical ventilation
**D**	Days when the patient is at risk for delirium	≥ 2 delirium screening assessments using a validated pediatric delirium screening tool
**E**	All days	Documentation of mobility goal AND highest level of mobility achieved each day
**F**	All days	A family member was educated on PICU Up! and/or participated in rounds/conferences/mobility

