The primary analysis for all outcomes will be unadjusted, that is, we will assume that patients enrolled in the study over time will be similar with respect to characteristics associated with the outcomes (e.g., age and severity of illness). Secondary analyses will include exploratory analyses to evaluate this assumption and the models (described above) will be extended to include an adjustment for key patient characteristics (e.g., age, admission diagnosis category, measures of baseline function such as PCPC, POPC, FSS). Analyses to detect significant differences in the intervention effect among sex/gender will be conducted. Additional secondary analyses will fit the models described above, including adjustment for the patient-specific measure of PICU Up! performance by separately including the measure of proportional performance (ranging from 0 to 1) and the binary indicator of a complete performance.

Statistical significance will be set at *p*-value < 0.05 using a two-sided hypothesis test for the primary outcome analysis; all secondary analyses will be considered exploratory with two-sided 95% confidence intervals reported. We will conduct missing data assessment/estimation, and if necessary, employ methods for imputation of missing data using the MICE package [50].

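### The performance-adjusted outcome models use a post-baseline covariate whose due elements and window depend on ventilation time, so neither its coefficient nor the adjusted period coefficient can be read as an effect

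*Protocol article*

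**What the plan says.** The primary outcome is the "number of days alive and ventilator-free (AVF) within the first 21 days after intubation", or after PICU admission for children intubated at another hospital. The main model has a period indicator, a random site intercept and a spline for month.

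Under Patient-level outcomes the article then states: "Additional secondary analyses will fit the models described above". Two refits are planned, each with one added performance term. The first is worded as "including adjustment for the patient-specific measure of PICU Up! performance by separately including the measure of proportional performance" (scaled 0 to 1); the second uses "the binary indicator of a complete performance". Because those models are refitted, the period indicator stays in beside the performance term.

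Table 2 (Process evaluation) sets when each element is due. Element B is due on "Days when receiving invasive mechanical ventilation", C on sedated and/or ventilated days, D on days at risk for delirium, and A, E and F on all days. Data collection and management ends collection at the earlier of day 21 or PICU discharge.

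On status, the article says "all secondary analyses will be considered exploratory with two-sided 95% confidence intervals reported". The 5% level applies "using a two-sided hypothesis test for the primary outcome analysis".

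**The concern.** A child's performance score builds up over the PICU stay. How many elements fall due, and over how many days, depends on how long the child is ventilated and stays in the unit. Ventilation time also generates days AVF. The plan therefore regresses the outcome on a quantity that is partly a consequence of it, and the article names no landmark, time-varying or causal method to deal with this.

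Two results are at stake. The performance coefficient invites the reading that better delivery does, or does not, shorten ventilation. The period coefficient next to it invites the reading of an intervention effect corrected for adherence. Either can be several tenths of a day to several days away from zero when nothing is going on.

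**Working it through.** The article gives no figure for this analysis and no element delivery rates. All rates below are assumptions. The anchors from Sample size and power calculation are a mean (variance) of days AVF of 13.2 (26.4), and 90 intervention cluster-months x 8 = 720 intervention patients.

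**1. Two children, no effect of performance.** Let V be ventilated days and let each child have 3 further PICU days, so days AVF = 21 - V. Take V = 4 (17 days AVF, 7 PICU days) and V = 14 (7 days AVF, 17 PICU days).

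- *Complete on every PICU day*, daily completion p = 0.9: the probability is p^days, so 0.9^7 = 0.48 against 0.9^17 = 0.17. The child ventilated for less time is more often complete.
- *Complete on at least one day*, p = 0.1: 1 - 0.9^7 = 0.52 against 1 - 0.9^17 = 0.83. The direction reverses.
- *Proportional.* For simplicity let D be due every day and let there be no sedation off the ventilator. With rate b for B and C and rate o for A, D, E and F, the expected proportion is [(2b + 4o)V + 4o x 3] / (6V + 12):

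| b | o | V = 4 | V = 14 |
|---|---|---|---|
| 0.60 | 0.85 | 28.6/36 = 0.794 | 74.6/96 = 0.777 |
| 0.90 | 0.70 | 26.8/36 = 0.744 | 72.8/96 = 0.758 |
| 0.80 | 0.80 | 0.800 | 0.800 |

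Unequal rates tie the proportion to V, in either direction. Equal rates do not.

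**2. Binary indicator over a whole population.** Ventilation time T is lognormal (log-mean 1.74, log-SD 0.77, T at least 2 days), PICU days = min(ceil(T + 2), 21), and a child is complete with probability p^days. Simulated AVF mean and variance are close to the stated values (12.7 and 25.3 when whole days are counted). Mean days AVF, complete minus not complete:

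| p | 0.9 | 0.8 | 0.7 | 0.5 |
|---|---|---|---|---|
| Difference | 3.10 | 3.59 | 3.92 | 4.50 |

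About 6% of children are complete at p = 0.7 and 0.8% at p = 0.5, so the last figure compares a very small group with the rest. A separate simulation applied the Table 2 rules element by element (AVF mean 12.9, variance 29.0; 720 patients; 500 replicates; between-patient SD of delivery 0.5 on the logit scale). It gave +3.4 to +4.5 days, with rejection 0.99-1.00 at nominal 0.05. If any complete day suffices, it gave -1.7 to -4.3 days; the largest value comes from a setting where almost every child qualifies.

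**3. Proportional measure, same element-level simulation.**

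| Assumed rates | Days AVF per 0.1 | Rejection |
|---|---|---|
| All 0.80 / all 0.95 | 0.03 / -0.06 | 0.05 / 0.05 |
| B, C 0.60; others 0.85 | +0.42 | 0.62 |
| B, C 0.90; others 0.70 | -0.31 | 0.43 |
| All 0.80, easier off the ventilator (+1 logit) | +0.85 | 0.98 |

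The less that children truly differ in delivery, the larger the artefact. Runs under other assumed spreads gave about -0.7 to +1.4.

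**4. Period coefficient.** With no intervention effect, and control-period odds of delivery assumed at 0.3 of the intervention period's, the unadjusted coefficient is about 0. After proportional adjustment it is -0.86, +0.75 and -1.71 days in the three unequal settings of step 3, and about 0 with equal rates.

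**5. Candidate remedies.** With performance restricted to days 1-3, the proportional slope is -0.02 to 0.01 per 0.1 with rejection 0.05-0.07. The complete indicators reject at 0.05-0.12, the higher values where the indicator is sparse. Same-month PICU performance does not help: with no PICU differences in delivery, it still gave about +1.2 to +1.3 and -0.8 to -0.9 per 0.1 in the two B/C settings. Only about 8 children contribute per month, and those ventilated longest contribute most days.

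**The case against.** The strongest reply is that fewer due elements do not by themselves raise a proportion, because numerator and denominator shrink together. That is correct. A reader might infer that the plan is bound to produce a false finding that better delivery shortens ventilation. The document does not support that: with equal rates the proportional slope is about 0, and with unequal rates its sign depends on rates the article does not give. Delivery and site also shape the score, so ventilation time only partly determines it.

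The size for the binary indicator rests on an assumed patient-level definition. The article defines complete performance only as a monthly PICU share of patient days. The full protocol or SAP may define it for patients, so its absence here is not itself a fault.

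A reader might also infer that the period coefficient becomes the effect of an intervention period with zero performance, because the article says "We will summarize the outcome of PICU Up! performance at the PICU level for each month of the intervention period". That sentence describes the PICU-level process summary. Elsewhere the article says data collection is the same in both phases. Whether control patients receive a score cannot be settled from the text. On either reading the coefficient is not the total effect defined for the main model.

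Finally, the analysis is exploratory, and the article nowhere calls it a dose-response analysis or says sites will act on it. This limits the severity. The label does not remove a bias built into the covariate, and a confidence interval would be centred on the wrong value.

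**Conclusion.** The concern holds in limited form. The planned covariate is post-baseline, and its denominator and window depend on the ventilation time that defines days AVF. With no true effect, an all-days-complete indicator shows about 3.0 to 4.5 more days AVF, and an any-day indicator shows a deficit. The proportional measure shows about -0.7 to +1.4 days per 0.1 when delivery differs between B/C and the other elements, or between ventilated and other days, and about 0 otherwise. These sizes rest on assumed delivery rates, coma and sedation frequencies, and stay after extubation. The 1.8-day detectable difference gives only a sense of scale, since it is a trial-level contrast and these are subgroup contrasts or slopes.

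The adjusted period coefficient does not estimate the intervention effect. The unadjusted primary analysis does not use the covariate and is untouched. The change should be made, but the trial's main conclusion does not depend on it.

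**What to change.** Measure patient performance, both proportional and complete, over a fixed early window and relate it to days AVF counted after that window. PICU days 1-3 would serve, since enrolment requires at least 48 h of invasive ventilation on day 3 and every included child is then ventilated. State how the patient-level complete indicator is formed. State that the period coefficient of any performance-adjusted model will not be reported as the intervention effect.

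Do not substitute same-month PICU performance that includes the patient's own days, because it carries the same artefact. If a PICU-level measure is wanted, leave out the index patient's days.

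The cost is analysis wording only, as the daily data are already collected. The landmark reflects early delivery only and is less precise. It removes the built-in dependence on ventilation time but not confounding by severity, so the result remains an observational association.

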#### Process evaluation

Online survey data will be summarized using descriptive statistics. The mean and standard deviation will be reported for continuous measures and frequency and percentages for categorical variables. Trends in performance within a PICU over time will be explored using spaghetti plots with locally weighted regression smoothers to explore the general trends over time across all PICUs. Mixed-effects Poisson models will be used to model the trends in performance over time via restricted cubic splines with a minimum of a random intercept defined at the PICU level. Subsequently, the models will include the hospital and PICU-level covariates, such as structural characteristics, staffing patterns, organizational traits, rounding practices, and the use of daily teamwork tools. The inclusion of such covariates will allow for the determination of whether variation in performance across the PICUs is partially explained by these PICU-level factors.

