### Objectives

The objective of the study is to evaluate if the PICU Up! intervention, delivered in real-world conditions, decreases mechanical ventilation duration (primary outcome) and improves delirium and functional status compared to usual care in critically ill children. A secondary objective is to conduct a multi-stakeholder, mixed-methods process evaluation to identify key contextual factors associated with the delivery of PICU Up!.

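### PICU Up! performance is a bounded proportion, but its trends are modelled as Poisson with no variance correction stated; trend intervals and, at high performance, the between-PICU variance are misestimated (minor)

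*Protocol article*

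**What the plan says.** Under Outcome measures, Process evaluation, performance is summarised per PICU and month: "We will summarize the outcome of PICU Up! performance at the PICU level for each month of the intervention period". Complete performance is "the proportion of patient days (for eligible patients) in which every eligible element of PICU Up! was performed". Proportional performance is "the proportion of eligible elements received divided by the number of eligible elements". Individual-element performance is likewise days on which the element was received over days on which it was eligible. Under Statistical methods, Patient-level outcomes, the proportional measure is given a range of 0 to 1.

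Under Statistical methods, Process evaluation, the model family is fixed: "Mixed-effects Poisson models will be used to model the trends in performance over time via restricted cubic splines". One random effect, an intercept per PICU, is required, and more are allowed. Hospital- and PICU-level covariates are then added to see whether they account for part of the variation between PICUs. This serves the secondary objective in Objectives, a "process evaluation to identify key contextual factors associated with the delivery of PICU Up".

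That section names no offset, dispersion term or robust variance. Robust variance and logistic mixed models are both mentioned, but only under Patient-level outcomes.

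**The concern.** All three measures are successes out of a known number of trials. A Poisson model lets the variance equal the mean and, with its usual log link, puts no ceiling on the fit at 1. The mismatch grows as performance rises, so it is largest where the programme is delivered well.

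Two results are exposed. The first is the interval around each PICU's trend in performance over time. The second is the estimated variance between PICUs: if the model attributes too much of the spread to sampling noise, it leaves too little for staffing, rounding practice and similar factors to explain. The article names the model family outright, so this is a stated choice and not a detail left to another document.

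**Working it through.** **Inputs from the article.** 10 PICUs; 21 months each; 3-month implementation; five steps of two PICUs; 8 eligible patients per cluster per month; 90 intervention months; 720 intervention patients.

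**Assumptions, because the article gives no figure.** Performance p from 0.3 to 0.9; 10 eligible days per patient; intervention lengths of 15, 12, 9, 6 and 3 months by pair (the design figure is not available); the between-PICU and between-child spreads stated below.

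**1. The plan's own base.** 10 x (21 - 3) = 180 PICU-months. Intervention months are 2 x (15 + 12 + 9 + 6 + 3) = 90, and 90 x 8 = 720 patients. Both figures reproduce. One PICU-month then holds 8 x 10 = 80 patient-days, and an average PICU with 9 intervention months holds 9 x 80 = 720 patient-days.

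**2. Trend standard errors, independent days.** The variance of a log proportion is 1/(np) under Poisson and (1-p)/(np) under binomial, so the SE ratio is 1/sqrt(1-p): 1.20 at p=0.3, 1.41 at 0.5, 1.83 at 0.7, 2.24 at 0.8 and 3.16 at 0.9. A nominal 95% interval would cover 98.1% at p=0.3, 99.4% at 0.5 and over 99.99% at 0.8.

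**3. Allowing for days clustered within children.** With design effect D the true variance is D(1-p)/(np). Poisson is then right by chance when D = 1/(1-p), that is 2 at p=0.5, 5 at 0.8 and 10 at 0.9. Below that its intervals are too wide; above it they are too narrow.

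Simulation: 90 PICU-months, 8 patients x 10 days, PICU logit SD 0.6, performance rising over the first months around the nominal p. The fit was Poisson with a log-denominator offset, PICU indicators standing in for the random intercept, and a restricted cubic spline. The ratio of Poisson SE to robust SE was:

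| nominal p | independent days | child logit SD 1 | child logit SD 2 |
|---|---|---|---|
| 0.3 | 1.33 | 0.90 | 0.67 |
| 0.5 | 1.53 | 1.00 | 0.76 |
| 0.7 | 1.87 | 1.24 | 0.88 |
| 0.8 | 2.33 | 1.51 | 0.98 |
| 0.9 | 3.29 | 2.09 | 1.22 |

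The first column lies a little above the formula in step 2, so read these as approximate.

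**4. Values above 100%.** For one PICU-month of 80 days, the Poisson upper limit is p x exp(1.96/sqrt(80p)). At p=0.8 this is 0.8 x exp(0.245) = 1.02, against 0.87 from a binomial logit interval. At p=0.9 it is 0.9 x exp(0.231) = 1.13, against 0.95. In the simulation, upper limits passed 1 in 9.7% of PICU-months at p=0.8 and 33.5% at p=0.9 with independent days, falling to 4.6% and 19.6% with child SD 1. Fitted means passed 1 in at most 1.2% of PICU-months.

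**5. Between-PICU variance.** Poisson overstates each PICU's sampling variance by 1/(np) - (1-p)/(np) = 1/n, and the fitted between-PICU variance drops by about that amount. With n=720, 1/n = 0.00139. A PICU logit SD of 0.5 is about 0.5(1-p) on the log scale.
- p=0.9: true variance 0.05^2 = 0.0025; fitted about 0.0025 - 0.00139 = 0.00111, or 0.44 of the truth.
- p=0.8: true variance 0.1^2 = 0.01; fitted about 0.0086, or 0.86.
- p=0.5: true variance 0.25^2 = 0.0625; fitted about 0.0611, or 0.98.

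A simulation of 150 datasets per scenario with a Poisson random-intercept model gave 0.45 at p=0.9 and 0.89 at p=0.8 with independent days, and 0.36 and 0.78 with child logit SD 1. At p=0.9 the estimate fell to near zero in 35% and 43% of runs respectively.

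**6. PICU-level covariates.** With between-PICU log SD t and 720 days per PICU, the SE ratio is sqrt[(t^2 + 1/(720p)) / (t^2 + (1-p)/(720p))]. For p from 0.5 to 0.9 it is 1.02 at t=0.2, 1.06 to 1.07 at t=0.1, and 1.17 to 1.23 at t=0.05. These hold t at its true value. If the fit lowers t^2 as in step 5, the two errors largely cancel: at p=0.9, 0.00111 + 0.00154 = 0.00265, and the binomial total is 0.0025 + 0.00015 = 0.00265. So 1.2 is nearer a ceiling than a typical value.

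**The case against.** The strongest reply has four parts.

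First, the objective concerns contextual factors measured at PICU level. With 10 PICUs their precision is governed by differences between PICUs, not by the sampling model for days. This stands. A reader might infer that intervals for the site factors are two to three times too wide; step 6 does not support that.

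Second, size and direction rest on a performance level and a within-child correlation that the article does not give, and several plausible settings come out close to correct. This stands too, so no single error factor can be claimed. It does not rescue the choice, because a reader could not tell which way a given interval errs.

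Third, the plan sets a PICU random intercept only as a minimum. A reader might infer that correlation of days within a child is ignored, but the wording leaves a child effect open. Further random effects can only add variance, however, so they cannot cure a Poisson variance that is already too large.

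Fourth, Poisson for a count with a log-denominator offset and robust variance is an accepted route to ratios of proportions, and those details may sit in a document not shown. That is fair for the trend standard errors. It would not restore the between-PICU variance, which comes from the Poisson likelihood itself.

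A reader might also take the unbounded log link to mean that fitted performance will often exceed 100%. Fitted means rarely did; upper confidence limits are the realistic problem, and mainly at high performance.

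**Conclusion.** The point holds as a minor one. The stated family does not match the stated outcome, and the section that fixes it adds no variance correction. For within-PICU trends, model-based standard errors are 1.4, 2.2 and 3.2 times too large at p=0.5, 0.8 and 0.9 if days are independent, and about 0.7 to 2.1 times the right size under moderate to strong within-child clustering. At p=0.9, upper limits above 100% become common, and the between-PICU variance is roughly halved under the assumed PICU logit SD of 0.5 and 720 days per PICU; at p=0.8 the loss is about 10 to 20%, and at 0.5 it is negligible.

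Inference on PICU-level covariates is little affected. The primary outcome analysis is untouched, since it is a separate linear mixed model of ventilator-free days.

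**What to change.** Under Statistical methods, Process evaluation, replace the Poisson family with one of these, keeping the splines and covariates:
- a binomial (logit) mixed model on patient-day data, with random intercepts for PICU and child; for proportional performance the denominator is the day's eligible elements; or
- a beta-binomial mixed model on monthly numerators and denominators.

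The child effect or extra-binomial term is needed. In a separate simulation with child logit SD 1 (about 9 children per month, 3 to 15 days each), a plain binomial model without it gave standard errors of only 0.64 to 0.69 of the true spread of the month slope.

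If Poisson is kept to obtain ratios, state a log-denominator offset and a robust or dispersion-corrected variance, and note that this does not correct the between-PICU variance.

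The cost is a changed model statement and no new data, because performance is already defined from patient-days. The drawback is that odds ratios replace rate ratios; reporting marginal predicted proportions by month and by site factor deals with that.
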